## 6.0 Request for Waiver of Informed Consent

---

A Waiver of Informed Consent and a Waiver of Authorization is requested because this is a retrospective chart review that involves no diagnostic or therapeutic intervention, as well as no direct patient contact. Study staff are unable to obtain consent from study subjects because due to the international patient population of M. D. Anderson Cancer Center, it would be impractical to obtain informed consents from individual patients prior to beginning the protocol. Additionally, it would bias the study if it were restricted to only those patients that we were able to contact. It is not practical to conduct this research

without this waiver since the status of the patient is unknown, i.e. whether they are alive or deceased and it is difficult to trace the whereabouts of the patients. The following requests for waivers are attached to this protocol:

Request for Waiver of Informed Consent

Request for Waiver of Authorization to Use and Disclose Protected Health Information (PHI)

## **7.0 Data Confidentiality:**

---

Data will only be available to the PI and people directly involved with the collection and analysis of data related to this project.

Collection of Identifiers: Identifiers (name, medical record number) will be collected but will be replaced by study numbers in the analytic file. The key linking these numbers will be retained in a locked file by the investigator designated personnel

Training of personnel: Only MDACC personnel designated by the Principal investigator will have access to study records. These personnel will be fully trained to maintain the patient health information confidential.

Data Storage: The PI and research staff will attempt to minimize risk through only storing information containing subject identifiers in locked file storage, on password-protected computers, and/or in password protected databases. In addition, access to patient identifiers will be limited to the minimum number of necessary research personnel, and only to those research personnel directly involved with obtaining patient information and assigning random study identifiers. Hard-copy information containing subject identifiers will be properly destroyed, using secured-information disposal sites and total-destruction shredding equipment to assure that subject privacy and confidentiality are protected. Keys containing information linking study subjects to personal identifiers will be maintained in locked storage and available ONLY to the PI and research personnel directly involved in creating random study identifiers. Information containing subject personal identifiers will not be removed from MD Anderson Cancer Center and will not be shared in publications or reports concerning this research study.

Data Sharing: Study data will not be shared with any individuals or entities that are not involved in the study.

Sample Management: Physical samples from this study will be obtained from protocol PA11-0670. Samples will be identified by a unique study identifier. PHI will be obtained in order to be able to match samples to data. The linking key between the sample identifier and the patient PHI will be retained by the PI on a secured, encrypted computer behind an institutionally approved firewall. Information from the PI Key will NOT be shared outside of

MD Anderson, but may be shared with study Co-PIs and research personnel who require it to facilitate study tests and assign test results.

Final disposition of study records: These data will be used only for this research study. Study data, paper records will be destroyed within 10 years after termination of the study.

## I. BACKGROUND

Pancreatic cancer is a disease that commonly afflicts older Americans and is often associated with frailty, a syndrome characterized by progressive loss of function along with the development of disability, malnutrition, and possibly impaired cognition. Frailty can be clinically identified according to clinical criteria including self-reported physical exhaustion, weak grip strength, weight loss, slow walking speed, and low physical activity [1]. Like age and comorbidity, frailty has been associated with adverse outcomes following pancreatic surgery [2].

By addressing the clinical manifestations of frailty, rehabilitation measures have been used in an attempt to improve outcomes of patients with pancreatic cancer who undergo potentially curative surgical resection. Rehabilitation regimens have typically been instituted following surgery. Home-based, postoperative rehabilitation programs as simple as structured walking regimens have been found to improve post-surgical outcomes [3].

Although postoperative rehabilitation programs may be successful, a growing body of scientific evidence supports the optimization of health, performance and nutrition of cancer patients *prior to* the initiation of anticancer therapies. **Cancer prehabilitation** represents a process on the continuum of care that occurs between the time of cancer diagnosis and the beginning of acute treatment, includes physical and psychological assessments that establish a baseline functional level, identifies impairments, and provides targeted interventions that improve a patient's health to reduce the incidence and the severity of current and future impairments [4]. Prehabilitation interventions have been used to decrease morbidity, improve physical and psychological health outcomes, increase the number of potential treatment options, decrease hospital readmissions, and reduce both direct and indirect healthcare costs attributed to cancer [4].

We currently administer chemotherapy and/or chemoradiation, followed by a preoperative rest period, to most patients with potentially curable pancreatic cancer prior to intended pancreatectomy [5, 6]. One of the primary goals of this approach is to select patients with both physiology and tumor biology most appropriate for surgical resection. For our patients with potentially curable pancreatic cancer, the preoperative therapy period provides a perfect time window within which a formal prehabilitation program could be used in an attempt to improve perioperative and oncologic outcomes. Treatment tolerance and fatigue that affect exercise program adherence (and thus feasibility) may vary across chemotherapy, chemoradiation, and the preoperative rest period. To date, no formal rehabilitation program has been established or evaluated in these preoperative settings for patients with potentially resectable pancreatic cancer.

### **Prior Data from MD Anderson Cancer Center**

Our group evaluates over 150 patients with resectable pancreatic cancer each year, of whom 80% receive preoperative therapy and would be considered potential candidates for this study.

We have completed a prospective study of the incidence of frailty among patients with pancreatic cancer at our institution. As part of this study, 26% of patients with pancreatic cancer of any stage met Fried Criteria for frailty [1]. Furthermore, the study, which

required completion of both the frailty assessment and a number of different survey tools (including those included in the present study) accrued rapidly with no real barriers to accrual identified in this patient population.

## **II. OBJECTIVES**

### **Primary Objective:**

To establish the feasibility of instituting a home-based, provider-supervised “prehabilitation” program during neoadjuvant chemotherapy and chemoradiation and preoperative recovery among patients with potentially curative pancreatic cancer at a quaternary care institution.

### **Secondary Objectives:**

- To assess the feasibility and compliance of nutrition intervention among these patients.
- To assess patients’ tolerance for specific exercises and ability to advance the exercises.
- To assess patients’ overall ability to complete study materials.

## **III. STUDY ENDPOINTS**

- 1) **Primary Endpoint:** Feasibility, based on adherence to the exercise intervention
- 2) **Secondary Endpoints:** Adherence to the nutrition intervention and completion of study materials.

## **IV. INCLUSION CRITERIA**

- 1) Pancreatic adenocarcinoma, biopsy-proven or suspected
- 2) Scheduled for intended pancreatectomy, > = 6 weeks until planned resection
- 3) Scheduled for neoadjuvant chemotherapy and/or chemoradiation for pancreatic cancer
- 4) Able to understand the description of the study and willing to participate.
- 5) Able to understand the exercise intervention and able to maintain a daily exercise log.
- 6) Participant must have telephone access and agree to engage with telephone access with the research personnel.

## **V. EXCLUSION CRITERIA**

- 1) Non-English speaking
- 2) Unable to complete the baseline assessment questionnaires or functional assessments
- 3) Underlying unstable cardiac or pulmonary disease or symptomatic cardiac disease (New York Heart Association functional class III or IV).
- 4) Recent fracture or acute musculoskeletal injury that precludes the ability to weight bear fully on all 4 limbs in order to participate in an exercise intervention.
- 5) Numeric pain rating scale of  $\geq 7$  out of 10
- 6) Myopathic or rheumatologic disease that impacts physical function

## VI. STUDY PLAN

### Schema

[figure not shown]

### Pre-Enrollment Screening

Patients will have a history and physical exam performed by the enrolling physicians to determine potential eligibility for the protocol. All patients in the surgical oncology clinic who are believed to be eligible will then be screened for enrollment to this trial using the *Physical Activity Readiness Questionnaire (PAR-Q)* and the first question of the Patient Reported Outcomes Measurement Information System (*PROMIS*) *Physical Function 12a Short Form*.

### PAR-Q Screening

- Patients who affirmatively answer questions 2, 3, 4 on the PAR-Q will be ineligible for enrollment.
- Patients who affirmatively answer questions 1 or 6 on the PAR-Q will require clearance by an internal medicine physician (co-PI or other) prior to enrollment. Most patients who are surgical candidates will be referred to the Internal Medicine Perioperative Assessment Center (IMPAC) Clinic close to

their pre-enrollment screening visit, as a part of routine, standard care. If they have been seen by IMPAC already, the medical co-PI will evaluate the IMPAC note and make a decision as to appropriateness for enrollment. If they have not been seen by IMPAC yet, the medical co-PI will evaluate the patient or facilitate any already scheduled IMPAC evaluation and make a final decision thereafter.

- Patients who affirmatively answer question 5 on the PAR-Q will require clearance by a PM&R physician (co-PI or other) prior to enrollment.
- Patients who affirmatively answer question 7 will require clearance by a co-PI prior to enrollment.

#### PROMIS Physical Function 12a Short Form Screening

- Patients who negatively answer the PF\_Screener question will be ineligible for enrollment.

#### ***Final Enrollment***

All patients will be consented prior to conducting any study related procedure and will be enrolled after they have met all screening and inclusion/exclusion criteria. At that time, the *FACT-Hep* quality of life instrument and baseline frailty assessment will be administered.

Frailty will be assessed using validated criteria, and defined as an abnormality in 3 or more of 5 markers [1]: 1) low physical activity, by self-report using *the International Physical Activity Questionnaire short form*, 2) exhaustion, by self-report using a score of 2 or 3 on either of two exhaustion items from the Center for Epidemiologic Studies Depression Scale (CES-D), 3) weight loss, defined as a loss of 3 kilograms in the prior 3 months, 4) weak grip strength, using a hand-held dynamometer and based on age- and gender-based normative values, and 5) slow gait speed, based on a cutoff of 3.2 seconds or more to complete a 3-meter walk.

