- The preoperative period varies in terms of both the types of treatments that patients undergo and the length of therapy. Approximately 70% of patients with technically resectable tumors undergo chemotherapy (6-12 weeks) followed by chemoradiation (2-6 weeks) and then a recovery period (4-6 weeks) before surgery. Approximately 20% of patients undergo chemoradiation (2-6 weeks) and then a recovery period (4-6 weeks) before surgery. Approximately 10% of patients undergo chemotherapy (6-12 weeks) and then a recovery period (4-6 weeks) before surgery. The exercise intervention will be performed throughout the treatment course.

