#### ***Nutrition intervention***

Within 7 days of enrollment, a registered dietitian (RD, ie the study dietitian or delegate RD) will conduct a complete nutritional assessment. Each subject will be then be provided with individualized recommendations for calorie, protein, and fluid intake, tools for tracking intake (ie, diet log), as well as goals for weight maintenance, weight gain, or weight loss depending on stage of treatment/recovery. Patients will also be instructed to eat a high protein snack/meal/shake (~20 g) within one hour after strengthening exercises.

As is current “standard of care” for our patients who undergo pancreatic surgery, all patients will also receive instruction on the use of an immune enhancing oral supplement (Impact Advanced Recovery) for 5 days preoperatively (preop days 6 through 1).

When the research staff contacts the participants via telephone to monitor their exercise program, they will also be asked questions regarding their compliance with the nutritional plan. The research staff will be provided with a list of questions to assess patient understanding of and ability to comply with nutrition recommendations. If patients are non-compliant or have difficulty comprehending the nutritional program, the RD will be notified and RD will follow up with the patient for reeducation or adjustment of goals. To monitor compliance with immune enhancing oral supplement, the patient/family will be interviewed following surgery to determine consumption.

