## **VII. Statistics**

This is a pilot study to assess the feasibility of a provider-supervised prehabilitation program among pancreatic patients who are undergoing neoadjuvant therapy. The prehabilitation program will include both exercise and nutrition interventions, where the exercise intervention will incorporate resistance/strengthening and walking programs. Adherence will be defined as the ability of each patient to complete  $\geq 60\%$  of the planned exercise intervention based on the total time spent performing the exercises relative to the total duration of therapy or total duration of recovery for a given phase. The primary endpoint, feasibility, will be established if  $\geq 60\%$  of the patients are adherent during a phase of therapy. That is, the prehabilitation program is deemed as feasible during a specific phase of therapy if 60% or more of the participants complete at least 60% of the weekly prescriptions for 60 minutes of walking and 60 minutes of strengthening

exercises during that phase of therapy. The calculation will account for the potential difference in the length of therapy among patients. The target weekly total exercise hour will be 120 minutes (including 60 minutes of walking and 60 minutes of strengthening exercises), thus we can derive the total prescribed hour for a given patient in a given phase considering his/her total treatment or recovery duration for that phase. Then, based on the recorded total hours of exercise intervention for that patient, we can calculate the % of completion for that patient in a given phase. If the % is at least 60% for a phase, we would define that patient as “adherent” for that phase. For the primary analysis, we will analyze the % adherence by phase, where “phase” could be chemotherapy phase, chemoradiation phase or recovery phase. As a secondary analysis, we will further differentiate whether patients receive chemoradiation from start or chemoradiation is given following chemotherapy and analyze these two subgroups of patients separately. Similarly, we will differentiate patients in recovery phase based on the therapies they receive prior to the recovery (i.e., chemotherapy only, chemoradiation only or chemotherapy plus chemoradiation).

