Descriptive statistics, such as frequency (percentage) and median (range) will be used to summarize the data, including patient demographics, clinical features, comorbidity,

symptoms burden and quality of life. We will also summarize patients' tolerance for specific exercises, their ability to advance the exercises and the motivating/prohibiting factors for them to complete the study materials. The rate of adherence will be estimated for each phase, along with the exact 95% confidence interval. Similarly, the proportion of patients with frailty (i.e., abnormality in 3 or more of 5 markers), perioperative complications (yes/no; high/low grade) and physical/functional measures (yes/no for completing the 5x sit-to-stand test and the 6-minute walk test) will be estimated, along with the exact 95% confidence intervals. As an exploratory analysis, we will fit a multiple logistic regression model to assess the association between patient characteristics and socioecological characteristics (social support for exercise and neighborhood walkability) and adherence (yes/no) for each phase. In addition, paired t-test or Wilcoxon signed rank test will be used to assess the change of Fact-Hep, Frailty, physical functioning, and exercise capacity measures from baseline. We will also fit a linear mixed model to assess the change of each measurement over time (i.e., at enrollment, pre-op and post-op visit), while accounting for the correlation among multiple observations from the same patient.

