### ***Study Measures***

Frailty will be measured based using validated criteria, and defined as an abnormality in 3 or more of 5 markers [1]: 1) low physical activity, by self-report using the International Physical Activity Questionnaire short form, 2) exhaustion, by self-report using a score of 2 or 3 on either of two exhaustion items from the Center for Epidemiologic Studies Depression Scale (CES-D), 3) weight loss, defined as a loss of 3 kilograms in the prior 3 months, 4) weak grip strength, using a hand-held dynamometer and based on age- and gender-based normative values, and 5) slow gait speed, based on a cutoff of 3.2 seconds or more to complete a 3-meter walk.

Perioperative complications will be prospectively graded and recorded using the modified Accordion scale [9, 10].

Pancreatic ductal adenocarcinoma (PDAC) Clinical Features: Additional clinical disease characteristics will be determined based on laboratory studies (albumin, prealbumin, c-reactive protein, creatinine, bilirubin, serum CA 19-9).

Demographic factors will include age, sex, race/ethnicity, place of residence, and presence of a primary caregiver.

Comorbidity will be determined prospectively using the Adult Comorbidity Evaluation-27 (ACE-27), a validated grading system that is predictive of prognosis in other cancer populations.

Symptom burden and quality of life (QOL) will be assessed using the Functional Assessment of Cancer Therapy-Hepatobiliary (FACT-Hep) quality of life and symptom index.

Physical functioning measures and exercise capacity: PROMIS SF v1.0 – Physical Function and 5x sit-to-stand test and 6-minute walk test

Lean body mass as measured by Slice-o-matic version 5.0.

Treatment side effects and fatigue: Participants will complete 2 items from the FACT-Hep daily, included on exercise logs. These items include GP5 ("I am bothered by side effects of treatment") and H17 ("I feel fatigued").

Physical activity will be measured using both objective monitoring and self-report.

Objective physical activity: Participants will undergo 2 weeks of objective monitoring using Actigraph GT3X accelerometers during each phase of neoadjuvant therapy (chemotherapy and/or chemoradiation and the preoperative recovery period) to measure total, light, and moderate-to-vigorous physical activity.

Self-reported physical activity: Participants will report physical activity using the IPAQ short form (administered as part of the frailty assessment) and in daily exercise logs.

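### The planned test of change in frailty includes two markers that following the program can move, so a change at the pre-op visit may partly reflect participation (minor; feasibility endpoint unaffected)

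*Protocol*

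**What the plan says.** All references are to the prehabilitation protocol (2014-0702).

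- **Definition.** Section VI, Final Enrollment, repeated under Study Measures in section VII: frailty is "defined as an abnormality in 3 or more of 5 markers". The five are activity, exhaustion, weight loss, grip strength and gait speed.
- **Activity marker.** "low physical activity, by self-report using the International Physical Activity Questionnaire short form". No cut-off for low is given. Study Measures also names the same questionnaire as a self-report measure of physical activity.
- **Weight marker.** "weight loss, defined as a loss of 3 kilograms in the prior 3 months". Intent is not mentioned.
- **Exercise.** Section VII: "The target weekly total exercise hour will be 120 minutes", split equally between walking and strengthening. Section VI, Exercise Intervention: "The exercise intervention will be performed throughout the treatment course".
- **Nutrition.** Section VI, Nutrition intervention: the dietitian gives each patient "goals for weight maintenance, weight gain, or weight loss depending on stage of treatment/recovery".
- **Analysis.** Section VII: a "paired t-test or Wilcoxon signed rank test will be used to assess the change of Fact-Hep, Frailty" and other measures from baseline. A linear mixed model covers enrollment, pre-op and post-op. There is no comparison arm.

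Nothing in the protocol separates prescribed exercise from the activity marker or intended loss from the weight marker.

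**The concern.** The frailty count is used as an outcome, yet two of its components overlap with what the study asks patients to do. A patient with exactly three abnormal markers, one of them low activity, can become non-frail by reporting the prescribed exercise while grip, gait, exhaustion and weight stay as they were. In the other direction, a patient with two abnormal markers who loses 3 kg toward a dietitian-set goal can become frail.

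With one arm, no control group shows how much of a change comes from taking part and how much from a change in strength, speed or fatigue. At stake is the reading of a supporting result: a reported improvement, or worsening, in frailty could be taken as a change in physical capacity when it is partly a record of participation.

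**Working it through.** **1. Does the program act in the period the markers look at?** Section VI gives phase lengths of 6–12 weeks for chemotherapy, 2–6 for chemoradiation and 4–6 for recovery. Adding them:

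- all three phases (about 70% of patients): 6+2+4 = 12 to 12+6+6 = 24 weeks
- chemotherapy then recovery (about 10%): 6+4 = 10 to 12+6 = 18 weeks
- chemoradiation then recovery (about 20%): 2+4 = 6 to 6+6 = 12 weeks

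Three months is about 13 weeks. In the commonest pathway, nearly all or all of the weight look-back at the pre-op visit lies inside the program. In the shortest, part of it precedes treatment. The exercise prescription runs up to surgery, so it covers the run-up to the pre-op activity report. It does not plainly cover the post-op visit.

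**2. How far could one marker move the composite?** The protocol states no figure for this, so there is none to reproduce. Its only frailty rate is 26%, from an earlier institutional study of patients at any stage (section I). Assume five equally prevalent, independent markers with prevalence p. Then P(Bin(5,p) ≥ 3) = 0.26 gives p = 0.3657.

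Let one marker have prevalence a and leave the other four alone:

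F = P(Bin(4,p) ≥ 3) + a × P(Bin(4,p) = 2) = 0.1420 + 0.3228a

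- Baseline, a = 0.3657: F = 0.260
- Activity marker halved, a = 0.1828: F = 0.201
- Activity marker cleared in all, a = 0: F = 0.142
- Goal-directed 3 kg loss in 10% of those not already abnormal on weight, a = 0.3657 + 0.1 × 0.6343 = 0.4291: F = 0.280
- The same in 30%, a = 0.5560: F = 0.321

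**3. Relaxing independence.** With a one-factor probit correlation among the markers, recalibrated to 26% each time:

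| Only change made | Corr. 0 | Corr. 0.3 | Corr. 0.5 |
|---|---|---|---|
| Activity marker halved | 20.1% | 21.7% | 22.3% |
| Activity marker cleared in all | 14.2% | 17.2% | 18.9% |
| Weight marker added in 10% | 28.0% | 27.7% | 27.6% |
| Weight marker added in 30% | 32.1% | 30.9% | 30.4% |

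From a 10% baseline, full clearing of the activity marker gives 4.9–6.6%. Adding the weight marker in 10–30% gives 11.4–14.7%.

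**4. Can the net effect be signed?** Take activity prevalence a and weight prevalence w, with the other three markers independent at p:

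F = P(Bin(3,p) = 3) + P(Bin(3,p) = 2) × [1 − (1−a)(1−w)] + P(Bin(3,p) = 1) × aw = 0.0489 + 0.2545 × [1 − (1−a)(1−w)] + 0.4414aw

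Hold w = 0.5560 (30% added):

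- activity marker cleared in all, a = 0: F = 19.0%, below 26%
- activity marker reduced by a quarter, a = 0.2743: F = 0.0489 + 0.2545 × 0.6778 + 0.4414 × 0.1525 = 28.9%, above 26%

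The sign depends on two shares that the protocol does not give.

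**The case against.** The strongest reply is that more activity is a real change and an intended one. Section I presents rehabilitation as acting on the manifestations of frailty and lists low activity among them. This stands: the activity marker belongs in the composite and should stay there. It does not answer whether anything other than the prescribed behaviour moved.

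A related reply is that no marker is free of the program, since it trains strength and walking and aims to be tolerable with respect to fatigue. That also stands. But grip and gait are measured performance, whereas the activity marker is a report of the behaviour prescribed. Marker-level reporting avoids having to declare some markers clean.

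A reader might infer that following the program clears the activity marker by definition. The document does not support this: no questionnaire cut-off is stated, so it cannot be shown that 120 minutes a week, or 60% of it, crosses the threshold.

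A reader might also infer that patients who comply with the dietitian will be scored frail. Loss is one of three possible goals, and neither its size nor the share of patients given it is stated. Goals of maintenance or gain push the marker the other way.

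Finally, change in frailty appears in no objective or endpoint (sections II and III). The same sentence of section VII also tests quality of life, physical functioning and exercise capacity, so physical condition is not read from frailty alone. This holds the severity down. Extra tabulations may also be left to an analysis plan that is not shown, but the definition of the weight marker and its silence on intent are fixed here in the protocol.

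**Conclusion.** The point holds at minor severity. The composite contains one marker that can shift directly with the prescribed exercise, and one that scores intended and unintended loss alike while the study may set a goal of loss. A change in frailty status at the pre-op visit can therefore partly reflect following the program.

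Size and net direction cannot be determined from the document. The 26% to 14–19% figures rest on equal marker prevalence, assumed correlations of 0 to 0.5, and complete clearing of one marker. They describe a yes/no rate, whereas the planned tests are a paired t-test or signed rank test. The 26% comes from a less selected population than participants here, who are surgical candidates screened for physical function. It would be wrong to read the figures as a projection for this trial.

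It would also be wrong to conclude that the trial's main result is compromised. Feasibility is judged on exercise adherence by phase, and neither that endpoint nor the sample size uses the frailty count.

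**What to change.** - **Final Enrollment and Study Measures:** state that the weight marker counts only loss that was not intended, and record at each assessment whether a loss was a dietitian-set goal. Study Measures does not list the goal as a data item, so its capture needs to be added. Intent should be judged for the loss itself, so that disease-driven loss in a patient who happens to have a loss goal is still counted.
- **Section VII:** keep the three-of-five result as the main frailty analysis. Beside it, report change marker by marker and a sensitivity result without the activity marker.
- **Interpretation:** do not describe a change in frailty as a change in physical capacity unless the other markers also move.

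The cost is one more data item and one more table, and the apparent change in frailty may be smaller. Limiting the weight marker to unintended loss alters the criteria slightly. With intent recorded, the count on the present wording can still be produced for comparison with the earlier institutional rate.
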